## Rationale and objectives

The overall objective of the present trial is to enhance the potential of ED prevention in children and adolescents (C&A) with an elevated risk for the development of an ED. Therefore, based on the latest scientific evidence outlined above, two new intervention modules will be added to the existing Internet-based ED prevention program ProYouth.

The first module will follow a dissonance-based ED prevention approach that was introduced in the context of the program with the best empirical evidence to date, i.e., the Body Project [24]. The Body Project is a group intervention to reduce thin-ideal internalization and subsequent ED symptoms using an approach based on cognitive dissonance assuming that adolescents and young adults develop body dissatisfaction and weight/shape concerns because of their internalization of the thin ideal (i.e., extremely thin women are considered most attractive/beautiful in Western societies). The rationale for the intervention is that participants who engage in exercises questioning this ideal should benefit from the program. Questioning the thin ideal thereby would reduce thin-ideal internalization, which should subsequently lead to a reduction of ED risk factors (e.g., body dissatisfaction, weight/shape concerns, dieting, and negative affect) and symptoms. The efficacy of the Body Project in terms of a reduction of ED risk factors, symptoms, and illness onset was shown in a number of large-scale randomized controlled trials (RCTs) (e.g., [24]). More recently, Internet-based versions of dissonance-based interventions have been introduced [25, 26].

The second module to be evaluated in this trial is based on a CBT approach. Several programs for selective ED prevention are based on CBT principles (see [11] for an overview), such as the well-studied program Student Bodies [27]. For the present trial, a clinician-guided group-based approach will be used. Promising findings have been reported both for the face-to-face as well as for an online chat-based delivery of such an approach in samples of Australian women with high levels of body dissatisfaction. However, existing findings are preliminary due to small sample sizes [28].

Following the development of these two new intervention modules and their implementation within the existing Internet-based program ProYouth, the specific objectives of the present trial focus on the efficacy and health economic evaluation of these enhanced versions compared to ProYouth alone.

## Methods/design

### Design and setting

The present trial represents one of five sub-projects conducted within the German multicenter consortium ProHEAD (Promoting Help-seeking using E-technology for ADolescents). Collaborators at five sites join forces in order to recruit a large representative school-based sample (*N* = 15,000) as part of the central project (CP) of ProHEAD. The five sub-projects are nested within this CP.

The present study (sub-project 2 of the ProHEAD Consortium) is a three-arm, parallel, randomized controlled superiority trial investigating the efficacy and cost-effectiveness of two new intervention modules for C&A at risk for the development of EDs in comparison to an active control intervention. The ethical committee of the Medical Faculty of Heidelberg University has approved the study procedures and design.

### Participants

Male and female C&A aged 12 years or older (grades 6–13) are invited to participate in the school-based ProHEAD screening. Those who provide informed consent (student and at least one legal guardian) and complete the screening will be assigned to one of the five ProHEAD sub-projects depending on their screening results (sub-project 1: clinically relevant mental health problems [29]; sub-project 2: risk for ED; sub-project 3: risky alcohol use [30]; sub-project 4: risk for depression [31]; sub-project 5: no clinically relevant mental health problems [32]).

Eligibility criteria are checked as part of the screening procedure. Inclusion criteria for the present trial are sufficient German language skills, Internet access, a high risk for an ED (Weight Concerns Scale (WCS; score > 57 [33, 34]) or sub-threshold ED symptoms based on the Short Evaluation of Eating Disorders (SEED [35]; bingeing and/or vomiting at least once a week). Individuals are excluded if they meet criteria for clinically relevant impairment as defined for sub-project 1 of ProHEAD [29]. This means that exclusion criteria for the present trial are severe ED symptoms, indicated by a body mass index (BMI) below the 5th percentile (adjusted for age and gender) and concurrent fear of weight gain, or daily bingeing, or daily vomiting assessed with the SEED [35]. Additional exclusion criteria include current suicidality, high depressive impairment measured with the Patient Health Questionnaire-9 modified for Adolescents (PHQ-A; score > 9 [36, 37]), high alcohol consumption assessed with the Alcohol Use Disorders Identification Test (AUDIT; score ≥ 20 [38]), and clinically relevant general psychological impairment operationalized with the Strengths and Difficulties Questionnaire (SDQ Total score ≥ 20; SDQ Emotional Symptoms score > 6; SDQ Conduct Problems score > 4; SDQ Hyperactivity score > 6; SDQ Peer Relationship Problems score > 5 [39, 40]).

Criteria for the allocation of participants to the five individual ProHEAD randomized controlled trials (RCTs) are based on the latest scientific evidence. However, this is the first time that the overall algorithm screening for various mental health problems is simultaneously applied on a consortium-wide basis. Therefore, an intermediate data analysis will be conducted following completion of 10% of the screening assessments (*N* = 1500) in order to determine the actual allocation ratio to the five ProHEAD trials and to adjust the screening algorithm if necessary.

### Recruitment and study procedures

The ProHEAD Consortium will recruit a school-based sample of 15,000 C&A aged 12 or older in grades 6–13 in five regions of Germany (Hamburg, Heidelberg, Leipzig, Marburg, Schwäbisch Gmünd). The procedures with respect to selection of schools are described in the study protocol of sub-project 1 of the ProHEAD Consortium [29].

Written informed consent will be obtained from C&A and their legal guardians prior to inclusion into the project. As part of the ProHEAD CP, assessments of sociodemographic information, healthcare utilization, help-seeking, and a broad variety of mental health problems and health-risk behaviors will be included in the screening and the two annual follow-ups. These three annual assessments will be conducted electronically via the ProHEAD online platform in the computer rooms of the respective schools (for details on the instruments used at the school-based assessments, see the study protocols of the other ProHEAD sub-projects in this issue [29–32]). Based on the screening results, each participant will be allocated to one of the five ProHEAD RCTs. Participants who meet eligibility criteria for more than one RCT will be randomly allocated to one of the sub-projects.

Participants assigned to the present ED trial will receive an email inviting them to register for the study. In order to enroll, they will need to click on a link in this email to activate their user account and to complete a trial-specific baseline online assessment. Upon completion of this assessment, they will be randomized to one of the three study arms and then have access to the respective intervention (ProYouth, ProYouth-DISS, or ProYouth-GROUP) for a duration of 6 weeks. Trial-specific post and follow-up assessments will be conducted online 6 weeks after randomization and 6 months later (Fig. 1).

**Fig. 1 Fig1:**
[figure not shown]
Participant flow diagram. Notes: *C&A* children and adolescents, *BMI* body mass index, *WCS* Weight Concerns Scale, *SP2* sub-project 2, *SP1* sub-project 1 [29], *CP* ProHEAD central project

Participants who complete the post-assessment after 6 weeks (primary outcome) will receive an online gift voucher (20€).

There is no obvious risk for participating C&A. Participation in the trial does not restrict utilization of conventional healthcare (e.g., counseling, treatment, medication), and information on where to seek help in case of ED-related and/or mental health problems will be provided for all participants. Use of standard healthcare services will be assessed in detail as part of the 12 and 24 months follow-ups in the school-based assessments of the ProHEAD CP.

Figure 2 shows the schedule of enrolment, interventions, and assessments of the present trial in detail. The recommended Standard Protocol Items: Recommendations for Interventional Trials (SPIRIT) 2013 checklist with items to address in clinical trial protocols is provided as Additional file 1.

**Fig. 2 Fig2:**
[figure not shown]
Schedule of enrolment, interventions, and assessments. Notes: –*t1* prior to participation, *Sociodemograph.* sociodemographic characteristics, *WCS* Weight Concerns Scale, *EDE-Q* (Child version of the) Eating Disorder Examination-Questionnaire, *SEED* Short Evaluation of Eating Disorders, *GHSQ* General Help-Seeking Questionnaire, *USS* Universal Stigma Scale, *SATAQ-G* German version of the Sociocultural Attitudes Towards Appearance Questionnaire, *BSQ-8C* 8-item version of the Body Shape Questionnaire, *ZUF-8* German version of the Client Satisfaction Questionnaire

### Randomization and blinding

Eligible C&A will be randomized to one of the three interventions based on an allocation sequence derived from a computerized random number generator at a 1:1:1 ratio. The allocation scheme is embedded into the ProHEAD online platform; i.e., participants are automatically assigned to one of the study arms and informed electronically about the outcome without researchers having access to the allocation scheme. Randomization will be stratified by gender. Due to the study characteristics, blinding of participants and/or online counselors is not possible because participants will be informed as to which intervention they were assigned, and counselors need to provide guidance accordingly.

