#### ProYouth-DISS

A structured dissonance-based intervention will be provided as an add-on to ProYouth; i.e., participants will have access to an enhanced version of ProYouth for 6 weeks. The ProYouth-DISS intervention aims at reducing ED risk factors by inducing cognitive dissonance. This approach assumes that the thin ideal and thin-ideal internalization play a major role in the development of ED. Internalized thin ideals in combination with social comparison processes result in increased body dissatisfaction. High levels of body dissatisfaction can cause dieting, restrained eating, and other compensatory measures to reduce body weight. This can be considered one of the developmental pathways of ED. ProYouth-DISS aims at counteracting these processes by influencing the internalized thin ideal and other weight- and shape-related beliefs and attitudes. As part of the intervention, participants will be asked to actively criticize such dysfunctional attitudes and beliefs. The discrepancy between the participants’ own beliefs and attitudes and the position they are representing in this situation causes dissonance. Because of the human tendency to seek consistency between attitudes and behaviors, this dissonance is reduced by a change of beliefs and attitudes (e.g., thin-ideal internalization, body dissatisfaction). Female participants will learn to challenge the thin ideal. In addition, they will be asked to engage in exercises aimed at reducing body image concerns. Male participants have access to an adapted version of ProYouth-DISS that challenges the muscular body ideal [42]. Videos with peers guide participants through the program and motivate them to attend the sessions. Participants work through the materials individually and may interact with a counselor on demand. The module consists of six sessions. As part of the weekly ProYouth monitoring emails, participants will be reminded to complete the ProYouth-DISS sessions. In addition to the structured ProYouth-DISS module, participants are encouraged to use the standard ProYouth modules.

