#### ProYouth-GROUP

A clinician-guided CBT group intervention will be provided as an add-on to ProYouth. The preliminary efficacy of CBT interventions in terms of reduction of body image problems and ED symptoms has been confirmed in both face-to-face and online settings [27]. Based on this evidence, the ProYouth-GROUP intervention will use a CBT approach to address factors that contribute to the development and maintenance of body dissatisfaction, weight/shape concerns, and disordered eating. A specific focus will be on environmental risk factors such as stigmatization and the perceived pressure from peers and media to conform to social appearance ideals. This pressure is assumed to increase both the internalization of social appearance ideals and body comparison tendencies, which subsequently lead to an increase of body dissatisfaction, weight/shape concerns, and disordered eating. Therefore, the ProYouth-GROUP intervention will teach skills for understanding and counteracting such pressures from peers and media and convey ways how to normalize one’s own eating behavior. The group chats focus on topics such as media influences on body dissatisfaction, strategies to improve self-esteem and body image, and emotion regulation skills. In addition, participants are asked to engage in cognitive behavioral exercises following each session. The last session will highlight the importance of seeking help early, discuss barriers to help-seeking, and illustrate strategies on where and how to seek professional help. The intervention consists of six 90-min group chat sessions facilitated by a qualified psychologist. Separate groups will be established for female and male participants. Videos with peers guide participants through the program and motivate them to attend the chat sessions. They are also reminded to join the chat sessions as part of the weekly ProYouth monitoring emails. In addition to this structured module, participants are encouraged to use the standard ProYouth modules.

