### Secondary outcomes

Secondary outcomes include ED symptomatology at 6, 12, and 24 months follow-up measured with the ChEDE-Q and the SEED. Additional outcomes are body dissatisfaction, appearance ideal internalization, ED-related stigma, and ED-related help-seeking at the end of the intervention and at 6 months follow-up. Body dissatisfaction is measured with the 8-item version of the widely used Body Shape Questionnaire (BSQ; [44, 45]). Research on the brief version (BSQ-8C) demonstrated good psychometric properties and sensitivity to change [46]. Items are rated on a 6-point Likert scale from 1 = “never” to 6 = “always”, with higher scores indicating higher levels of body dissatisfaction. Appearance ideal internalization is assessed using the internalization subscale of the German version of the Sociocultural Attitudes Towards Appearance Questionnaire (SATAQ-G) for female and male participants, respectively [47]. It consists of 6 items reflecting the adoption of the thin or muscular ideal as a personal standard. Stigma is measured with the ED-specific version of the Universal Stigma Scale (USS; [48]). The USS is an 11-item instrument. It consists of two subscales (impairment/distrust, blame/personal responsibility), with internal consistencies between 0.72 and 0.83 across different samples [48]. ED-related help-seeking is measured with an ED-specific version of the General Help-Seeking Questionnaire (GHSQ; [49]), a frequently used measure for help-seeking for psychological complaints. Acceptance of the online interventions (ProYouth, ProYouth-DISS, ProYouth GROUP) will be assessed with the German version of the Client Satisfaction Questionnaire (ZUF-8; [50]) adapted for the online setting. The ZUF-8 measures participants’ satisfaction with the intervention. Finally, compliance with the interventions and utilization of the various modules will be analyzed based on automatically recorded server logs.

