### Statistical analysis

Primary data analyses will be based on the intention-to-treat (ITT) population; i.e., all participants randomized to one of the three study conditions will be included in the primary outcome analysis. Missing data patterns will be explored. Multiple imputations will be applied to impute missing data.

Repeated measures ANOVA will be conducted (time*group interaction, alpha = 5%) to test the primary hypothesis, i.e., differences in efficacy between the interventions. For the primary outcome, only the baseline and the post assessment after 6 weeks will be considered. In case of statistically significant differences, post hoc pairwise group comparisons will be conducted (Bonferroni correction). Repeated measures ANOVA will also be conducted to determine the effect of the interventions on metric secondary outcomes. Post-intervention symptom courses will be analyzed applying mixed effects models. In order to investigate gender-specific efficacy, multifactor ANOVAs will be conducted. Fisher’s exact test will be applied to compare actual help-seeking between the groups.

For the health economic evaluation, data on the costs of interventions and efficacy will be used to determine the incremental cost-effectiveness ratio (ICER) of the interventions. The ICER will provide the additional costs in monetary terms of the respective programs to be spent for gaining an additional outcome unit. Cost-utility analyses will provide information on cost per quality-adjusted life years (QALYs) gained by the various interventions. Bootstrapping procedures will be applied to provide cost-effectiveness planes and acceptability curves.

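### Gender stratifies the randomisation but is absent from the stated primary model; the cost is small and conservative, and including it is almost free

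*Protocol article*

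**What the plan says.** All places are in the protocol article, under Methods/design.

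- Randomization and blinding: three arms, "an allocation sequence derived from a computerized random number generator at a 1:1:1 ratio", and "Randomization will be stratified by gender".
- Statistical analysis: "Repeated measures ANOVA will be conducted (time*group interaction, alpha = 5%) to test the primary hypothesis", and "For the primary outcome, only the baseline and the post assessment after 6 weeks will be considered". No gender term is named. Gender appears in one later sentence: "In order to investigate gender-specific efficacy, multifactor ANOVAs will be conducted".
- Sample size calculation: the trial is sized on the same time*group test, again without gender.
- Interventions: content or delivery differs by gender in both add-on arms. For the dissonance module, "Male participants have access to an adapted version of ProYouth-DISS that challenges the muscular body ideal"; for the chat groups, "Separate groups will be established for female and male participants".
- Secondary outcomes: the SATAQ-G internalisation subscale has a female and a male version. "It consists of 6 items reflecting the adoption of the thin or muscular ideal as a personal standard".

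**The concern.** A factor used to restrict the randomisation is normally carried into the analysis. If it is left out and it predicts the analysed quantity, its variance is counted as error although the design has balanced it across arms. The test is then conservative and some power is lost.

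Here the primary model is stated and the stratum is not in it. A gender difference in change is conceivable: boys in the dissonance arm work on a different body ideal, the chat groups are split by gender, and the Discussion says there is almost no prevention research in males. At stake is a little precision in the primary test, and agreement between the design and the analysis. SATAQ-G raises the same issue, because change scores from two versions of the scale would be pooled.

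**Working it through.** **Inputs from the documents.** Three arms; two visits (m = 2); alpha 5%; f = 0.15; correlation between visits rho = 0.1; dropout 20%; N = 309; 90% power.

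**Assumed, because the documents do not give them.** The share of boys p (20%, with a range of 10 to 50%), the size of any gender difference, and rho = 0.5 as a second value in step 5.

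**1. The plan's own figure.** For the time*group F test the noncentrality is lambda = f² x N x m/(1 - rho), with 2 and N - 3 degrees of freedom. The smallest N with 90% power is 257, where lambda = 0.0225 x 257 x 2/0.9 = 12.85. Then 257 x 1.2 = 308.4, rounded up to the stated 309. After 20% dropout, 309 x 0.8 = 247 are evaluable, lambda = 12.35 and power is 88.9%.

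**2. What the error term contains.** With two visits the time*group test is a one-way ANOVA on change. In baseline-SD units the within-gender variance of change is 2 x (1 - 0.1) = 1.80.

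- A gender gap that is equal at both visits cancels in the change and adds nothing.
- A gender difference in change of size delta adds p(1 - p) x delta². With p = 0.2, delta = 0.25, 0.5 and 1.0 give 1.81, 1.84 and 1.96.

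A simulation (82 evaluable per arm, gender balanced across arms, 3,000 runs per setting) agrees. With stable gaps of 0, 1 and 2 SD the error mean square is 1.80 with or without gender, and power (about 88 to 89%) is the same within 0.1 point. With the three differences in change it is 1.81, 1.84 and 1.96 without gender, against 1.80 with it.

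**3. Effect on power.** Let h be the gender difference in change, in within-gender SDs of change. Then R² = p(1 - p)h²/(1 + p(1 - p)h²), and including gender raises lambda to 12.35/(1 - R²), with 2 and 243 degrees of freedom.

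| h | R² (p = 0.2) | lambda | Power (p = 0.2) | Power (p from 0.1 to 0.5) |
|---|---|---|---|---|
| 0 | 0 | 12.35 | 88.9% | 88.9% |
| 0.2 | 0.0064 | 12.43 | 89.1% | 89.0 to 89.2% |
| 0.5 | 0.0385 | 12.84 | 90.1% | 89.6 to 90.7% |
| 0.8 | 0.0929 | 13.61 | 91.8% | 90.6 to 93.1% |

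The simulation gives a gain of the same order: at delta = 1.0, power was 87.8% without gender and 89.9% with it.

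**4. Type I error.** Without gender, the simulated rate stays near 5% and falls to 3.9% at delta = 1.0. With gender in the model, that case returns to 5.0%.

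**5. Gender in an ANCOVA.** In a model of the 6-week score on arm and baseline, a stable gap g does matter. With v = p(1 - p)g², residual variance is (1 + v) - (rho + v)²/(1 + v) without gender and 1 - rho² with it. For p = 0.2:

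- rho = 0.1, g = 0.5 (v = 0.04): 1.021 falls to 0.990, a reduction of 3%.
- rho = 0.1, g = 1.0 (v = 0.16): 1.102 falls to 0.990, a reduction of 10%.
- rho = 0.5, g = 0.5: 0.760 falls to 0.750, a reduction of 1%.
- rho = 0.5, g = 1.0: 0.784 falls to 0.750, a reduction of 4%.

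**The case against.** The strongest reply is that the plan's test is already protected. It works on within-person change, so a difference in level between girls and boys does not reach the error term. Omitting gender is valid and at worst mildly conservative. Stratification also balances the two SATAQ-G versions across arms, and a constant level difference between versions cancels in the same way. Nothing in the documents shows that the versions differ in scaling. The gender-specific content bears mainly on effect modification, for which separate ANOVAs are planned. Finally, this is a condensed article, and an analysis plan that is not shown may list the stratum.

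Most of this stands, and it limits the point to a small one. It does not remove it. The article names its primary model, visits and alpha, and bases the sample size on the same model, so this is a stated analysis without the stratum. The separate gender ANOVAs do not change the primary test. If an unseen analysis plan already includes gender in a form that acts on change, the point is met.

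A reader might infer that all between-gender variance inflates the primary error term, and convert the share of 6-week variance explained by gender into a number of participants wasted. The stated test does not support that: it does not use the cross-sectional 6-week variance, and stable differences drop out of it (step 2).

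**Conclusion.** The point holds as a minor improvement. Randomisation is stratified by gender, and the stated primary model omits it. With 20% boys, the gain from including it is zero for a stable gap and about 0.2 to 2.9 percentage points of power for a gender difference in change of 0.2 to 0.8 SD. The most extreme case examined (half boys, 0.8 SD) gives about 4 points. These sizes rest on an assumed share of boys and an assumed gender difference.

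The documents do not support a claim that the primary p-value would be anti-conservative. The error, if any, is on the safe side. The reason to change is that the analysis would then match the design at almost no cost.

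**What to change.** Put the stratification factor into the primary model and the metric secondary models in a form that acts on the tested effect. Either of these will do:

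- keep the repeated measures ANOVA and add gender and gender x time (a gender main effect alone leaves the time*group test unchanged); or
- use ANCOVA of the 6-week score on arm, baseline and gender, with the corresponding post-baseline score for secondary outcomes.

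The same term covers SATAQ-G, where it absorbs a mean difference in change between the female and male versions. Keep the planned multifactor ANOVAs as the separate analysis of gender-specific efficacy.

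The cost is a sentence in the analysis section and one degree of freedom in the tested stratum. No new data are needed, because gender must be known to randomise.
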